### Data collection

Cardiac consultations will take place before and at 6- and 12-months after surgery, during which patients will be given an ECG and monitored for incident hypertension, diabetes mellitus, and cardiovascular events (e.g., myocardial infarction, stroke). Fasting blood and urine samples will be collected before surgery (PSO or other pelvic) and at 1, 3, 6, and 12 months after surgery. In addition to routine blood tests (glucose, hemoglobin A1c), Calgary Lab Services will conduct the following analyses: lipid profile (total cholesterol, HDL, LDL, triglycerides) and a female endocrine panel (estradiol, progesterone, FSH, LH). Our research laboratory will separately analyze blood samples at these time points for assessment of novel cardiovascular biomarkers. Plasma will be extracted from blood samples, aliquoted, and stored at -80 °C for future testing (e.g., enzyme-linked immunosorbent assays for HSP27, HSP27 antibodies, PCSK9, as well as inflammatory cytokine arrays [performed by EVE Technologies on campus]). Urine samples will also be stored at -80 °C for future isolation of microparticles and exosomes (ultracentrifugation) and detection of HSP27 and PCSK9 (Western blot and mass spectrometry). Retinal images will be captured by digital photography before and at 6 and 12 months after surgery by a high-volume retinal referral clinic (Calgary Retina Consultants) and images will be securely transferred to the University of Wisconsin Retina Core lab for analysis (Drs. [name]). In addition to the above data collection time points, patients will be given the option of extending their participation for an additional year, which will involve cardiac consultations, blood draws, and retinal imaging at 18- and 24-months post-surgery.

To complement this work, our collaborator, [name] (MD Anderson, Houston; **W**omen choos**I**ng **S**urgical **P**revention “**WISP**” trial [ClinicalTrials.gov Identifier: NCT02760849] researcher) will also provide plasma samples before and after PSO in their cohorts diagnosed with BRCA- or Lynch syndrome-associated mutations (~ 35 WISP participants).

### Outcomes

The primary outcome is a change in levels of HSP27 following PSO. Plasma HSP27 will be measured using ELISA methods before and 1, 3, 6, and 12 months following surgery. Since previous findings have shown that higher HSP27 serum levels correlate with cardiovascular health [66], it is likely that women experiencing premature menopause after PSO will experience a worsening of their cardiovascular health (as measured by total cholesterol and LDL) and consequently, lower levels of HSP27. HSP27 localized to microparticles isolated from plasma and urine will also be measured using Western blotting and mass spectrometry. Additional primary outcomes assessed at the same time points and analyzed by ELISA are: HSP27 natural antibodies, which appear to be elevated in healthy controls compared to coronary artery disease patients, and PCSK9, which itself may be regulated by HSP27 (unpublished data). Secondary outcome variables are lipids (total cholesterol, triglycerides, HDL, LDL), ovarian hormones (estradiol, FSH, LH, progesterone), cytokines, and retinal vessel (arteriole and venule) diameters. Abnormally high lipid levels and/or severe post-menopausal symptoms following PSO may necessitate alterations in management and treatment by attending physicians.

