**Methods/Design:**

To manage CAD risk there is a prerequisite for reliable biomarkers that can help guide risk assessment and therapeutic interventions. To address these needs, this prospective, observational cohort study will evaluate surrogate markers reflective of CAD health in women experiencing surgical menopause after PSO. Twenty women representing each of the following groups will be enrolled over 3 years (total participants = 240): (i) pre-menopausal PSO, (ii) post-menopausal PSO, (iii) pre-menopausal women undergoing other pelvic surgery, and (iv) pre-menopausal controls (no surgery). All participants will provide blood plasma samples pre- and 1, 3, 6, & 12 months post-operatively, with serial samples collectively assessed for measurements of the study’s primary endpoints of interest. These include a hormone profile (estradiol, follicle stimulating hormone (FSH), luteinizing hormone (LH), and progesterone) and both conventional (lipid profile) and novel biomarkers (Heat Shock Protein 27 (HSP27), HSP27-antibodies (HSP27 Ab), proprotein convertase subtilisin/kexin 9 (PCSK9), inflammatory cytokines) of CAD. Another aspect of this study is the measurement and analysis of retinal vessel diameters – an emerging physiological parameter reflective of CAD risk. Finally, a patient engagement exercise will result in the drafting of patient-generated questionnaires that address the well-being and health concerns of these women as they transition through premature menopause and work with our research team to identify and discuss their health priorities.

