### Statistical analyses

Data analysis will be performed using Statistical Analysis System (SAS) software. Probability (p) of less than 0.05 will be considered significant. Experimental outcomes for continuous variables will be expressed as means ± standard deviation for each time point and the variance between the groups will be analyzed using ANOVA. Categorical variables will be compared with a chi-square test. In order to examine the relationship between variables, regression analysis will be performed. If more than one predictor variable is found to affect the outcome, multivariate regression will be employed to identify significant associations.

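### The primary outcome set contradicts itself, and three primaries under a single p<0.05 threshold raise the family-wise error from 5% to about 14% at one time point

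*Protocol article*

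**What the plan says.** The protocol article gives three different accounts of what is primary.

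- **One outcome.** The Outcomes section opens with: "The primary outcome is a change in levels of HSP27 following PSO".
- **Three outcomes.** The same paragraph goes on: "Additional primary outcomes assessed at the same time points and analyzed by ELISA are: HSP27 natural antibodies", "and PCSK9, which itself may be regulated by HSP27".
- **A much wider set.** The Abstract (Methods/Design) describes blood sampling "with serial samples collectively assessed for measurements of the study’s primary endpoints of interest" and then says: "These include a hormone profile (estradiol, follicle stimulating hormone (FSH), luteinizing hormone (LH), and progesterone) and both conventional (lipid profile) and novel biomarkers". The novel biomarkers it lists are HSP27, HSP27 antibodies, PCSK9 and inflammatory cytokines.

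The Outcomes section places most of that wider set elsewhere: "Secondary outcome variables are lipids (total cholesterol, triglycerides, HDL, LDL), ovarian hormones (estradiol, FSH, LH, progesterone), cytokines, and retinal vessel" diameters.

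On timing, the Outcomes section says: "Plasma HSP27 will be measured using ELISA methods before and 1, 3, 6, and 12 months following surgery". The four post-operative times are therefore named, but none is singled out as primary.

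On the decision rule, Statistical analyses says: "Probability (p) of less than 0.05 will be considered significant". It plans summaries at each time point and a comparison of groups by ANOVA. The Sample size calculation uses alpha 0.05 once, with power 0.90 and effect size 0.3, and does not say which outcome or time it refers to. It reuses alpha 0.05 for the planned recalculation from pilot data.

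**The concern.** A reader cannot tell from the article whether an LDL, FSH or cytokine result would be a primary or a secondary finding, or whether HSP27 stands alone or is one of three. Both sides of the conflict are printed, so condensing a longer protocol does not explain it.

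The labelling matters because the error rate depends on it. If any of three outcomes can deliver a positive primary result at an unadjusted 0.05, the 5% that the sample size section spends is no longer the error rate of the study's main claim. The minimum sample size was also computed for one test, so it would not give the stated power once the three tests were corrected.

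**Working it through.** **Inputs**

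- Four groups, alpha 0.05, power 0.90, effect size 0.3, minimum 160 (40 per group), 10% attrition, 178 after attrition: Sample size calculation.
- Recruitment target 240: Participant recruitment.
- Three primaries and four post-operative visits: Outcomes.
- Threshold 0.05: Statistical analyses.
- Assumed, because the article does not say: 0.3 is Cohen's f, and all correlations used below.

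**1. Reproduce the stated size.** Power of a one-way ANOVA comes from the noncentral F distribution with 3 and N−4 degrees of freedom and λ = N × f².

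- N = 160: λ = 160 × 0.09 = 14.4, power 0.897. Reaching 0.90 exactly takes 164 (41 per group), so 160 agrees to within rounding.
- Attrition: 160 / 0.90 = 177.8, rounded up to 178, as stated.
- Reading 0.3 as a two-group standardised difference would need 234 per group, which does not match. Cohen's f is the reading that fits.

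The stated size is therefore the size for **one** test at 0.05.

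**2. Family-wise error if no outcome truly differs.** For m independent tests at 0.05 the rate is 1 − 0.95^m.

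| Primary tests | m | Rate if independent |
|---|---|---|
| One outcome, one time | 1 | 5.0% |
| Three outcomes, one time | 3 | 14.3% |
| HSP27 alone, four visits | 4 | 18.5% |
| Three outcomes, four visits | 12 | 46.0% |

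**3. Allow for correlation in the 12-test case.** Repeated values in the same woman are correlated, so 46% is the independence figure. Simulated ANOVAs with four groups of 40 (10,000 runs per cell) gave:

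| Correlation between visits | Outcomes uncorrelated | Outcome correlation 0.3 | Outcome correlation 0.5 |
|---|---|---|---|
| 0.5 | 40.5% | 40.4% | 37.7% |
| 0.7 | 35.1% | 34.1% | 32.8% |
| 0.9 | 27.3% | 24.8% | 24.2% |

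The simulation standard error near 40% is √(0.4 × 0.6 / 10,000) ≈ 0.5 percentage points, so the range is about 24% to 41%.

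**4. Size and power if the error is controlled by Bonferroni (f = 0.3).** Completers from the planned 240: 240 × 0.90 = 216, or 54 per group.

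| Rule | Alpha per test | Power at 160 | Power at 216 | Completers for 0.90 | With 10% attrition |
|---|---|---|---|---|---|
| One primary | 0.05 | 0.897 | 0.969 | 164 | 183 |
| Three primaries, one time | 0.05/3 = 0.0167 | 0.796 | 0.923 | 204 | 204/0.90 → 227 |
| Three primaries, four visits | 0.05/12 = 0.0042 | 0.638 | 0.831 | 252 | 252/0.90 = 280 |

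The target of 240 covers three corrected primaries at one time. It does not cover twelve corrected tests.

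**The case against.** The strongest reply has four parts.

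- **Separate tests at each visit are not stated.** This is correct. The article plans summaries by visit and an ANOVA between groups. It specifies neither four visit-wise tests nor one model across visits, and a change in level can be a single comparison. A reader might infer that twelve primary tests at 0.05 are planned, but the text only leaves room for that. The 24% to 41% and 46% figures are therefore conditional.
- **A multiplicity rule and a primary visit may sit in a fuller document.** This is fair, and their absence alone is not the point here. What remains is what the article does print: conflicting primary lists, several outcomes labelled primary, one flat threshold, and a size computed for one test.
- **The Outcomes section can be read as one lead primary with two additions, for which 160/178 stands.** That reading is possible, and several primaries are a legitimate design. But the additions are themselves called primary, with no order or ranking, and this reading does nothing for the conflict with the Abstract.
- **The work is an observational pilot.** The article does call it pilot work with a small sample. It also sets alpha 0.05 and 90% power in confirmatory style, and its results are meant to inform larger studies.

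A reader might also infer that a false-positive primary result is likely. The figures do not support that: for three outcomes every rate is below one half. The Abstract's wider list (at least 11 outcomes, or 44 tests over four visits) would reach 89.5% under independence. That calculation assumes no outcome changes at all, whereas the article itself expects an abrupt loss of estrogen after surgery in pre-menopausal women.

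**Conclusion.** The contradiction is certain and rests only on the printed text: one versus three primaries within the Outcomes section, and hormones, lipids and cytokines primary in the Abstract but secondary in the Outcomes section.

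The effect on error is moderate. Family-wise error rises from 5% to about 14% for three primaries at one time, assuming independent outcomes and no true differences. Any larger figure depends on testing at every visit, which is not stated, and on correlations the article does not give.

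Once three primaries are corrected, the stated minimum of 160 has power of about 0.80 rather than 0.90, if 0.3 is Cohen's f. The planned 240 is still enough, so the problem can be resolved in the wording without enlarging the study.

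**What to change.** Before any results are seen:

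1. Name one primary outcome. HSP27 is the natural choice, since the Outcomes section opens with it.
2. Tie it to one pre-specified time or to one overall contrast across visits. Twelve months is one acceptable choice; nothing in the article requires it.
3. Test HSP27 antibodies and PCSK9 after it in fixed order, or call them key secondary outcomes.
4. Align the Abstract with the Outcomes section, so that hormones, lipids and cytokines are secondary in both.

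The stated 160/178 then stands.

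If three primaries are kept, apply Holm or Bonferroni across them at one named time or contrast. State that 0.3 is Cohen's f, if it is, and restate the minimum as 204 completers (227 with 10% attrition). Use the same corrected alpha when the sample size is recalculated from pilot data.

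The cost is a change of wording and a somewhat stricter hurdle for the added outcomes. Recruitment stays within the planned 240.

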### Sample size calculation

To date, there are no prospective studies investigating HSP27, HSP27 Ab, and PCSK9 levels in women following PSO and the ensuing premature, surgical menopause. To estimate the necessary sample size, we assumed an effect size of 0.3, Type 1 error rate α = 0.05, and desired power = 0.90. Based on our conservative assumptions, a minimal sample size of at least 160 participants (40 per group) is needed for the study. Assuming 10% attrition rate over the course of the study, a minimum of 178 participants will be required (which is well below our recruitment target of 240). Once there is sufficient enrollment (*n* = 6 / group), effect size will be recalculated based on pilot data (again presuming α = 0.05 and power = 0.90) and the sample size adjusted accordingly as the study continues.

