### Participant recruitment

Depending on family history and outcome of genetic testing, women that are positive for mutations in BRCA1/2 or Lynch syndrome associated-genes (e.g., HNPCC) may be referred by the University of Calgary’s team of genetic counselors for an information sharing consultation with gynecologists who specialize in minimally invasive PSO. During the medical genetics consultation, patients will be given a cursory introduction to this study via dissemination of an information pamphlet. After discussing with their gynecologist, who will further elaborate on the details of this study, patients who decide to undergo PSO and are interested in participating will then be scheduled for an appointment with a cardiologist ([name]). Post-menopausal women considering PSO and pre-menopausal women undergoing other pelvic surgeries will be introduced to the study by the same team of medical genetics counsellors and gynecologists, while non-surgical control participants will be enrolled through the use of recruitment flyers posted at the University of Calgary and its affiliated hospitals. Active patient enrollment for this study will take place over 3 years. Recruitment targets for each of the four patient treatment groups are 20 per year, totalling 240 participants for the duration of the study.

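### The sample size may be reset from the effect observed in 24 women, with no stated floor or direction; if it can fall below 40 per group, the planned power and error rate are not secured

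*Protocol article*

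**What the plan says.** The Sample size calculation section of the protocol article sets the basis: "we assumed an effect size of 0.3", with "Type 1 error rate α = 0.05" and "desired power = 0.90". It concludes that "a minimal sample size of at least 160 participants (40 per group) is needed for the study". It then allows for losses: "Assuming 10% attrition rate over the course of the study, a minimum of 178 participants will be required". Participant recruitment sets the target above this: "Recruitment targets for each of the four patient treatment groups are 20 per year, totalling 240 participants".

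The same section goes on to say that once 6 women per group are enrolled, "effect size will be recalculated based on pilot data", again for 5% error and 90% power, and "the sample size adjusted accordingly as the study continues". What is re-estimated is the effect size, not only the standard deviation. No lower limit, upper limit, direction or estimator is given for the adjustment. Statistical analyses compares groups by ANOVA at p < 0.05 and mentions no allowance for this look.

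**The concern.** A between-group effect size from four groups of six carries little information. The usual sample estimates are also too large on average, because chance differences among four small group means count as effect. If such an estimate replaces 0.3 and is treated as the truth, the required number tends to come out too low, and the study could stop well short of 40 per group.

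Two things are at stake. The first is power: the 90% claim belongs to 40 per group, not to whatever number the early data suggest. The second is the false-positive rate. If the early women stay in the final test, the study stops small when they happen to look different and carries on when they do not, which pushes an unadjusted 5% test above 5%.

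**Working it through.** **Inputs from the article.** Four equal groups; effect size 0.3; α = 0.05; power 0.90; 160 in all; 10% attrition; target 240 (60 per group); look at 6 per group (24 women); ANOVA at p < 0.05.

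**Assumptions not in the article.** The effect size is Cohen's f for a one-way ANOVA; one normally distributed endpoint; no dropout; the early women are kept in the final analysis; one group differs from the other three. At f = 0.3, a linear pattern of group means gave the same result where it was tried (eta-squared estimate, cap of 240).

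**Step 1: reproduce the planned size.** Power comes from the noncentral F distribution with 3 and N − 4 degrees of freedom and noncentrality λ = N × f².
- N = 160, f = 0.3: λ = 160 × 0.09 = 14.4, power 0.897.
- Reaching 0.90 exactly takes 41 per group (164), so 160 is reproduced to within 3%.
- Attrition: 160 / 0.90 = 177.8, rounded up to 178, as stated.
- Reading 0.3 as a pairwise d (234 per group) or a paired d (117) does not give 160, which supports reading it as Cohen's f.

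**Step 2: the estimate at 6 per group.** Two common plug-in formulas are f̂ = √(SSB/SSW), from the observed eta-squared, and f̂ = √((SSB/24)/MSE) with MSE = SSW/20. With unit variance, E(SSW) = 20 and E(SSB) = 3 + 24f². Ratios of these expectations show the bias:
- f = 0: √(3/20) = 0.39 and √(3/24) = 0.35. Simulated medians are 0.35 and 0.32, above 0.3 although no effect exists.
- f = 0.3: E(SSB) = 3 + 2.16 = 5.16, so √(5.16/20) = 0.51 and √(5.16/24) = 0.46. Simulated medians are 0.47 and 0.43. The 10th to 90th percentiles are 0.24–0.77 and 0.22–0.70.

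**Step 3: what that does to the number.** As a rough guide, N ≈ 14.4/f̂². For f̂ = 0.47 this is 65, about 16 per group; for 0.43 it is 78, about 19 per group. The exact noncentral F solutions at the medians are 18 and 21 per group, against 40 planned.

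**Step 4: simulate the rule.** Draw 6 per group, compute f̂, solve for n per group at 90% power, continue to that n (at most 60 per group), and test all women by ANOVA at 0.05.

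| Reading of the rule | Recalculated below 40 per group, f = 0.3 | Power, f = 0.3 | Type I error, f = 0 |
|---|---|---|---|
| Fixed 40 per group | – | 0.90 | 5.0% |
| Plug-in estimate, no floor | 76–81% | 0.69–0.73 | 7.5–8.3% |
| Plug-in, at least 26 per group | same estimates | 0.81–0.83 | about 5.5% |
| Bias-corrected (omega-squared), no floor | 42% | about 0.88–0.89 | about 6.7% |
| Plug-in, increase only from 40 | none applied | 0.92–0.93 | 5.2–5.4% |

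With the plug-in estimates and no true effect, 53–61% of recalculations still fall below 40 per group. At a true f of 0.2, 65–71% do, although the need there is about (0.3/0.2)² = 2.25 times larger.

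**Where 26 per group comes from.** At an even 20 per group per year, six are enrolled after 6/20 × 12 = 3.6 months. Their 12-month samples arrive at about 15.6 months, when 20 × 15.6/12 = 26 per group have been enrolled.

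**The case against.** The strongest defence is that 160 and 178 are both called minimums and recruitment is set at 240, so the adjustment may be meant only to raise the number. On that reading both harms nearly vanish. The article does not say so, however: those minimums follow from the assumed 0.3, which is the very value the next sentence replaces, and the adjustment is given no direction.

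Three further points carry weight.
- **Lag.** Outcomes run to 12 months, so enrolment would probably have passed 6 per group by the time a 12-month result is known. If those women are kept, the damage is moderate. With 1-month data the lag is short. The article does not say which time point is used.
- **Estimator.** A bias-corrected estimate cuts the study in a minority of runs and roughly holds the power, although type I error still rises. No estimator is named.
- **Early women left out.** Excluding them from the final test would restore the 5% error rate. The reference to the study continuing points towards keeping them, and exclusion would not undo a sample that is too small.

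It is also fair that this is an observational cohort whose Discussion calls it pilot work and whose Study limitations section admits a small sample. The article names three primary biomarkers at several time points, so a simulation of one endpoint illustrates the rule and does not give the study's exact operating characteristics.

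A reader might infer that the rule will usually shrink the study whatever the truth, so that the 90% and 5% claims are lost. The document does not support that. It requires a free downward adjustment, an upward-biased estimator and an early stop, none of which the article states.

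**Conclusion.** The concern holds in a conditional form. The rule lets an effect estimate from 24 women replace the planning value and reset the size, and nothing in the text prevents a cut below 40 per group. With the usual estimators and no floor, power at f = 0.3 is about 0.7 and type I error about 8%. Other readings that the text allows range from a moderate loss of power to almost no harm. The fault is that the article fixes the rule without the floor or direction that decides between these outcomes. All figures rest on the assumptions listed in the working. For an observational study that describes itself as pilot work, this is something that should be fixed, not a fatal flaw.

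**What to change.** Either of two changes to the Sample size calculation section is enough.
1. Delete the effect-size recalculation and keep 178 enrolled as the minimum and 240 as the target.
2. Keep a re-estimation step, but state that 160 evaluable (178 enrolled) is a floor, that the step may only increase the sample, and that 240 remains the target.

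If a check on the assumptions is still wanted, re-estimate only the pooled standard deviation, without comparing groups, and apply the same floor.

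The cost is a few sentences. Neither change adds women to the plan, because recruitment to 240 is already intended.
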